#### Sample size

For sample size estimation, a difference in depression (i.e., primary outcome) between intervention and control group at follow-up of medium effect size is considered as clinically relevant (Cohen’s d = 0.5), which also corresponds to finding from a recent meta-analysis [8]. The sample estimation (test family: t-test for independent samples) with Gpower 3.1 [38] yielded an estimated minimum sample size of the two groups of *n* = 51 at a Type I error rate of alpha = 0.05 and a statistical power of 1-beta = 0.80 individuals. If a dropout rate of 20% is taken into account [39], as was the case in comparable studies, the final rounded sample size per group is *n* = 65, or *N* = 130 persons in total. While 20% of drop out is common in psychotherapy trails for older adults, considering the vulnerability of our sample of vulnerable participants, we will be collecting further participants to guarantee sufficient statistical power at follow up.

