## Methods/design

### Trial design

PSY-CARE is a single-center interventional study, using a pragmatic randomized controlled design with nested qualitative research, comparing individual psychotherapy with an active control condition. The intervention condition will include manual-guided psychotherapy provided by gerontologically trained resident psychotherapists [27]. The active control condition will include individual telephone counselling carried out by project staff members as well as a self-help guide for participants and their caregivers [28]. The flow chart of the study design is depicted in Fig. 1. The schedule of enrolment, interventions, and assessments is shown in Table 1.

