### Assignment of interventions

#### Allocation and blinding

Participants will be randomized to the two treatment arms. A computer-assisted randomization to either intervention or control condition with 1:1 ratio is performed by the method center, using R v3.2.1 [41, 42] and the package “blockrand” (block randomization with block sizes 4, 6, and 8). Stratifications is not undertaken. In order to ensure allocation concealment, central randomization is used at the participant level, where the recruiting person got sequentially numbered, opaque, sealed envelopes from the method center. The creation of the random assignment sequence, the enrollment participants and the assignment of the participants to the interventions will be strictly separated. The project staff involved in evaluating the results will be blinded to the intervention allocation.

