### Data collection, management and statistical analysis

Standardized assessments will be carried out at baseline, directly after the intervention and at a follow-up after 3 months. The quantitative assessment (Hypotheses 1 and 2) among participants will be carried out by two trained study nurses (clinical psychologists with advanced clinical training). The questionnaires will be conducted as computer assessed interviews using a secure laptop and will take up to a maximum of two hours per participant. Data collection will be monitored by the method center and later automatically transferred to SPSS v25 (IBM, Cary, Ind.). When selecting the measuring instruments, attention was paid to the objectivity, reliability, and validity of the assessments.

Psychotherapists will also complete questionnaires in paper-pencil format and later transferred to a SPSS v25 data mask. Missing data will be handled using multiple imputation. Furthermore, qualitative data will be collected from psychotherapists, gatekeepers and older participants. Data will be stored and analyzed at the method center. Only the evaluation team will have access to the data, as defined in the data protection concept as part of the ethics approval.

The evaluation based on participant data will be carried out by means of multivariate longitudinal methods (random effects models). Both intention-to-treat analyzes and completers analyzes will be carried out. A post hoc effectiveness analysis of three potentially moderating characteristics of those in need of care will be considered: (a) degree of cognitive impairment, (b) drug use, and (c) late-onset versus early onset depression. In addition to effect sizes, remission and response rates (Reliable Change Index; RCI) will be determined.

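### The sample size makes no allowance for participants sharing a psychotherapist, and the analysis description does not commit to a therapist term

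*Protocol article*

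**What the plan says.** Under Trial design, the intervention is "manual-guided psychotherapy provided by gerontologically trained resident psychotherapists". The Interventions section makes this individual treatment of up to 24 sessions. Recruitment of psychotherapists describes a pool of volunteer practitioners but gives neither its size nor the expected caseload. Control participants and their caregivers are each offered two telephone calls by project team members, plus self-help material (Interventions).

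The Sample size section states the method as "The sample estimation (test family: t-test for independent samples) with Gpower 3.1", "at a Type I error rate of alpha = 0.05 and a statistical power of 1-beta = 0.80", for a standardised difference of 0.5. This gives 51 per group, raised to 65 per group (130 in total) for 20% dropout. It mentions no ICC, design effect, therapist number or caseload. It also promises an unspecified number of further participants, on the grounds of dropout and the vulnerability of the sample.

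The analysis is by "multivariate longitudinal methods (random effects models"). Which effects are random is not stated.

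**The concern.** Outcomes of participants treated by the same therapist tend to resemble each other, because therapists differ in skill, style and the participants they take on. A two-sample t-test calculation assumes that this resemblance is absent. Individual randomisation does not remove it, since the sharing arises after allocation. A participant-level random effect for repeated measures does not remove it either, since it models correlation within a participant and not between participants.

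Two things are at stake. First, the stated 80% power is too high if there is any therapist clustering, whatever the final model contains. Second, if the final model has no therapist term, the standard error is too small and the false-positive rate exceeds its nominal level. The trial is pragmatic and asks what psychotherapy achieves in regular care, so its conclusion is meant to reach beyond the therapists recruited. Their variation therefore belongs in the error term.

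**Working it through.** **Inputs from the protocol article.** Standardised difference d = 0.5, alpha 0.05 (sidedness not stated), power 0.80, dropout 20% (Sample size); individual 1:1 randomisation (Allocation and blinding).

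**Assumed inputs.** Participants per therapist m = 2 to 10 and therapist ICC ρ = 0.02 to 0.10. Neither is in the article. Clustering in the control arm is set to zero here as a simplification.

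**Step 1: reproduce the plan's figure.** Exact noncentral-t power for two independent means with d = 0.5 and 51 per group is 0.806 one-sided and 0.706 two-sided. The smallest n reaching 0.80 is 51 one-sided and 64 two-sided. The plan's 51 is therefore a one-sided figure, and that basis is used below. Dropout: 51 / 0.80 = 63.75, so 64, which the plan rounds to 65.

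**Step 2: variance with clustering in the therapy arm.** With n per arm and total SD fixed at 1:

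- Design effect in the therapy arm: DE = 1 + (m − 1)ρ
- Variance of the difference: DE/n + 1/n
- Ratio to the independent case: R = (DE + 1)/2

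Middle case, m = 5 and ρ = 0.05: DE = 1 + 4 × 0.05 = 1.20, R = 1.10, and the true standard error is √1.10 = 1.049 times the naive one.

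**Step 3: type I error if therapist is ignored** (large-sample): 1 − Φ(1.645/√R). Middle case: 1 − Φ(1.645/1.049) = 1 − Φ(1.568) = 0.058.

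**Step 4: power when therapist is modelled.** Noncentral t with noncentrality 0.5/√(DE/n + 1/n) and Satterthwaite degrees of freedom

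df = (v₁ + v₀)² / [v₁²/(k − 1) + v₀²/(n − 1)], where v₁ = DE/n, v₀ = 1/n and k = n/m therapists.

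Middle case: v₁ = 1.20/51 = 0.02353, v₀ = 1/51 = 0.01961, k = 10.2. Then df = 27.4, noncentrality = 0.5/√0.04314 = 2.41, critical t = 1.702, power = 0.76.

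**Results at 51 analysed per arm, one-sided alpha 0.05** (80.6% power with no clustering):

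| m | ICC | Variance | SE factor | Type I error if ignored | df | Power |
|---|---|---|---|---|---|---|
| 2 | 0.02 | +1% | 1.005 | 5.1% | 65.3 | 80% |
| 5 | 0.05 | +10% | 1.049 | 5.8% | 27.4 | 76% |
| 5 | 0.10 | +20% | 1.095 | 6.7% | 24.7 | 72% |
| 10 | 0.05 | +22.5% | 1.107 | 6.9% | 11.3 | 69% |
| 10 | 0.10 | +45% | 1.204 | 8.6% | 9.3 | 62% |

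Part of the power loss comes from the fewer degrees of freedom. A normal approximation without that penalty gives 78% in the middle case and 67% in the last row.

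**Step 5: enrolment for 80% power.** By the same normal approximation, n per arm = [(1.645 + 0.842)/0.5]² × (DE + 1).

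- Middle case: 24.73 × 2.20 = 54.4, so 55 analysed, 69 enrolled per arm, 138 in total.
- m = 10, ρ = 0.10: 24.73 × 2.90 = 71.7, so 72 analysed, 90 enrolled per arm, 180 in total.

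The plan has 130. These totals leave out the degrees-of-freedom penalty and are therefore slightly low.

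**Limit.** With m = 1 or ρ = 0, nothing changes.

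**The case against.** **The model may already contain a therapist effect.** A reader might infer from the word longitudinal that the random effects cover repeated measures only, and conclude that the standard errors are too small. The article does not say this. It leaves the random-effects structure open, random effects models are where a therapist term would be fitted, and such detail commonly sits in an analysis plan, which is not shown here. This objection stands: understated standard errors are conditional and not demonstrated. It does not rescue the sample size, which is a completed calculation on independent participants. If the analysis plan does include a therapist term, the stated power is still too high.

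**Only one arm is clustered.** This too is tempting, but control participants share counsellors from the project team. With two calls offered to each participant, the effect is probably slight, but the article does not rule it out.

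**Power of 48% to 70%.** A two-sided calculation at 52 per arm (65 × 0.80) starts from 71% and falls to that range under the same assumptions. It would be wrong to blame therapists for the whole gap from 80%. The starting point of 71% reflects the unstated one-sided alpha, which is a separate matter.

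**The size is driven by assumptions.** This is fair. The top of the range needs about five therapists for the whole arm together with an ICC of 0.10, and nothing in the article points to so small a pool. At low caseloads the effect is trivial.

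**Further participants are planned.** They might absorb a shortfall of 8 (138 against 130), but the reserve has no number and is justified by dropout and vulnerability, not clustering.

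**Conclusion.** The point holds in a conditional form. The sample size assumes independence that the delivery of the therapy arm breaks wherever a therapist treats more than one participant, and the analysis description does not commit to handling it. On the plan's own one-sided basis, the assumed ranges (2 to 10 participants per therapist, ICC 0.02 to 0.10, no clustering in the control arm) give 1% to 45% more variance, power of about 80% to 62% instead of 80.6%, and a type I error of 5.1% to 8.6% if the therapist term is omitted. The middle case is a moderate loss: +10% variance, 76% power and 5.8% error. The article cannot place the trial within this range. The point is worth acting on because the planned number has almost no reserve: 65 × 0.80 = 52 analysed against a minimum of 51.

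**What to change.** - Record the treating psychotherapist for every therapy-arm participant, and the counsellor for every control participant.
- In the primary and secondary models, include a therapist random intercept for the therapy arm (a partially nested model) with Satterthwaite or Kenward-Roger degrees of freedom. Check for counsellor clustering in the control arm. If an existing analysis plan already does this, cite it.
- State the expected number of therapists, the caseload and the assumed ICC, and restate the power for the planned N on that basis, saying whether alpha is one- or two-sided.

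The cost is one identifier per participant and some wording in the analysis plan. The price is slightly wider confidence intervals and a lower stated power. The change is best made before outcome data are analysed by arm.

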### Objectives

PSY-CARE investigates the feasibility and effectiveness of individual outpatient psychotherapy within the regular German health care system for home-living older adults in need of care with clinically significant depression. Outpatient psychotherapy tailored to the specific needs of this population is provided based on a treatment manual by certified resident CBT psychotherapists with extensive professional experience in geriatric or geropsychiatric settings.

In terms of the effectiveness of the intervention, we hypothesized that psychotherapy leads to a greater reduction of depressive symptoms, which we considered the primary outcome, compared to an alternative intervention, which encompassed brief psychosocial counselling (Hypothesis 1). Further, we hypothesized that psychotherapy will be associated with a relative difference at follow-up in the secondary outcomes – i.e., quality of life, activities of daily living, functioning and subjective health – in the intervention condition compared with the control condition (Hypothesis 2). More specifically, we assume maintenance of activities of daily living and quality of life, and functioning/ subjective health in the intervention condition relative to the control condition, which we assume shows a decline. Further, in this trial treatment response (50% or greater reduction in depressive symptoms from baseline to follow up) and remission [defined as number of individuals who scoring below the cut-off of 10 points at the Geriatric Depression Scale (GDS; [25, 26] at follow up] will be used as secondary outcomes.

In terms of the feasibility of the intervention under the real conditions of the German health care system, a wide range of approaches to recruit participants of this hard-to-reach population is used and effective versus non-effective recruitment methods are documented. In addition, we aim to explore possibilities and constraints of psychotherapists’ clinical practice of working with home-living vulnerable older adults including their professional experiences with home treatment in case of participants’ limited mobility, as well as collaboration with other healthcare professionals, especially with general practitioners and formal or informal caregivers.

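### The 51 per group is the answer for a one-sided 0.05 test that the protocol never declares; a two-sided 0.05 test has about 71% power, not 80%

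*Protocol article*

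**What the plan says.** The Sample size section of the protocol article takes a between-group difference at follow-up "of medium effect size is considered as clinically relevant (Cohen’s d = 0.5") as its target. It names the method: "The sample estimation (test family: t-test for independent samples) with Gpower 3.1". The error rates are given as "at a Type I error rate of alpha = 0.05 and a statistical power of 1-beta = 0.80 individuals", and the calculation "yielded an estimated minimum sample size of the two groups of *n* = 51". Allowing for 20% dropout, the section arrives at 65 per group, 130 in total. Because the population is vulnerable, it adds that "we will be collecting further participants to guarantee sufficient statistical power at follow up", without a number or a rule.

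Sidedness is not given there, nor in the section on data collection, management and statistical analysis. The nearest statement is Hypothesis 1 in Objectives, which is worded in one direction: "we hypothesized that psychotherapy leads to a greater reduction of depressive symptoms".

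**The concern.** For d = 0.5, alpha 0.05 and 80% power, the familiar two-sided answer is 64 per group. A stated 51 is well below that. A reader who meets alpha = 0.05 without qualification will take it as two-sided and will believe that the trial has 80% power for its primary outcome.

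This calculation is the only justification given for N = 130. If the analysis is two-sided, the stated power is too high and a null result could be given more weight than it deserves. If the analysis is one-sided, the primary claim is tested at a threshold twice as lenient as readers will assume.

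**Working it through.** **Inputs.** From Sample size: d = 0.5, independent-samples t-test in G*Power 3.1, alpha = 0.05, power 0.80, n = 51 per group, dropout 20%, final n = 65 per group. From Allocation and blinding: 1:1 allocation. Sidedness: not stated, so both cases are computed.

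**Formula.** With n per group, the t statistic has 2n − 2 degrees of freedom and noncentrality δ = d·√(n/2). Power is the probability that this noncentral t exceeds the critical value: the 0.95 quantile of t if one-sided, the 0.975 quantile (plus the negligible opposite tail) if two-sided.

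**Reproducing the stated figure.**
- One-sided 0.05: n = 50 gives 79.9% and n = 51 gives 80.6%. The exact solution is 50.15, rounded up to 51. This matches the protocol.
- Two-sided 0.05: the exact solution is 63.77, rounded up to 64 (power 80.1%). This does not match.
- Cross-check by the normal approximation, n = 2(z₁ + z₂)²/d². One-sided: 8 × (1.645 + 0.842)² ≈ 49.5, so 50. Two-sided: 8 × (1.960 + 0.842)² ≈ 62.8, so 63. Each is one below the t-based answer, as expected.

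**Dropout step.** 51/0.8 = 63.75, hence 64, which the protocol rounds to 65. This step is sound. In reverse, 65 × 0.8 = 52 evaluable per group.

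**Power for d = 0.5.**

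| n per group | δ | one-sided 0.05 | two-sided 0.05 |
|---|---|---|---|
| 51 (stated minimum) | 0.5·√25.5 = 2.525 | 80.6% | 70.6% |
| 52 (65 less 20%) | 0.5·√26 = 2.550 | 81.3% | 71.4% |
| 64 | 0.5·√32 = 2.828 | 87.9% | 80.1% |
| 65 (no dropout) | 0.5·√32.5 = 2.850 | 88.3% | 80.8% |

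**Other ways to state the gap (two-sided 0.05).**
- Chance of missing d = 0.5 with 52 per group: 100 − 71.4 = 28.6%, against 20% claimed.
- Effect detectable with 80% power: d = 0.56 with 51 per group and d = 0.55 with 52.
- Number needed for 80% power at d = 0.5: 64 evaluable, so 64/0.8 = 80 randomised per group (N = 160). That is 15 per group more than the 65 planned.
- A two-sided test at alpha 0.10 also gives 51 per group, so the stated figure is equivalent to that design.

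**The case against.** The strongest reply is that nothing is miscalculated: 51 is exactly right for a one-sided test, Hypothesis 1 is directional, and only a word is missing, one that an unseen full protocol or SAP may supply. Part of this stands. The figure does reproduce, and a two-sided final analysis is an assumption because the article is silent. But a directional hypothesis is routinely tested two-sided and does not by itself declare a one-sided test. Nor is this just a detail left for later. The article reports a finished calculation whose alpha, power and n agree only under an unstated choice, and an SAP that specified a two-sided test would make the published justification wrong.

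Second, the planned analysis is a random-effects model over three time points, and using baseline could recover power. That is possible. With a baseline–follow-up correlation of 0.45, the two-sided requirement falls to about 64 × (1 − 0.45²) = 51, and power with 52 per group rises to about 81%. With a correlation of 0.3 it is about 75%, and with zero correlation it stays at 71%. The article gives no correlation, so these are assumed values. The sample size section claims no such gain and names a plain t-test, so the 71% should be read as the unadjusted figure.

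Third, the protocol already announces extra recruitment, so 52 evaluable is a base case and not a fixed end point. This too is fair, but the extra recruitment is explained by dropout beyond 20%, not by sidedness. It has no number, so it cannot be credited with closing a gap of 15 per group. The text does not suggest that outcome data would drive it. Bounding it is a secondary improvement, and the main point does not depend on it.

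**Conclusion.** The concern holds. The stated alpha, power and n are consistent only for a one-sided 0.05 test, which the article does not declare. Read as two-sided 0.05, power for d = 0.5 is 70.6% at the stated 51 per group and 71.4% at the 52 expected after 20% dropout. Read as one-sided, the power is as claimed, but the type I error corresponds to two-sided 0.10 and is not disclosed. The Sample size section needs correcting in either case.

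The 71% rests on 65 randomised per group, 20% dropout, and an unadjusted two-sample t-test at one time point. It would be higher if baseline adjustment helps or more participants are recruited, and lower if dropout exceeds 20%.

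**What to change.** - **Preferred:** state in Sample size and in the analysis section that the primary test is two-sided at 0.05. Restate the power for 65 randomised per group: about 71% for d = 0.5 with 52 evaluable per group, or 80% for d = 0.55, before baseline adjustment. If a gain from baseline adjustment is to be claimed, give the assumed correlation and the resulting power.
- **Alternative:** if a one-sided 0.05 test is intended, declare it in both places so that readers can see the error rate that applies.
- **In either case:** replace the open-ended sentence on further participants with a rule based only on pooled, blinded retention at T3 against a stated evaluable number, never on outcome data.

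The cost is protocol and SAP wording and a less favourable power statement. No extra participants are required. Restoring 80% two-sided power for d = 0.5 by recruitment alone would take 80 per group, and this fix does not ask for that.

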#### Recruitment of psychotherapists

The recruitment of resident psychotherapists who volunteer to participate in PSY-CARE is supported by the biggest Association for Behavior Therapy in Germany (German Society for Behavioral Therapy) and includes several offers in newsletters, online mailing lists and distribution of flyers. Certified CBT psychotherapists with extensive work experience in geriatric and/or geropsychiatric settings are included into the pool of PSY-CARE psychotherapists. In addition, they receive a two days training course, conducted by the principal investigator (PI) [40]. They will receive an expense allowance of €1000 for their participation in the study, in addition to their regular fees for psychotherapeutic services within the regular health care system.

#### Recruitment of participants and the treatment team

Recruitment takes place via self-referral as well as gatekeeper referral and uses a wide range of approaches including distributions of flyers and posters, public talks, presentations within institutions, advertisements in online newsletters of collaborating institutions in the health and care sector and media reports in newspapers and magazines. In addition, professionals working with vulnerable home-living older adults on a day-to-day basis in ambulatory care services, medical practices, geriatric and geropsychiatric clinics and counseling centers were recruited via phone call, e-mail or mail. Gatekeepers are given flyers and reminder letters to prompt referrals. In order to participate in the study, an informed consent sheet is signed and participants receive a copy of the signed documents. Neither participants nor gatekeepers will receive any direct financial compensation. The main caregiver of the participant (professional caregiver or family member) is included in the study, if the participants give their written consent for participation.

